#### Serious adverse events

A serious adverse event is any adverse event that results in any of the following outcomes:

- death
- is life-threatening (places the subject, in the view of the investigator, at immediate risk of death from the event as it occurred)
- inpatient hospitalization or prolongation of existing hospitalization (hospitalization is defined as an inpatient admission, regardless of length of stay, even if hospitalized as a precautionary measure for continued observation)
- a persistent or significant disability/incapacity (substantial disruption of the ability to conduct normal life functions)
- a congenital anomaly/birth defect
- a medically significant event that may jeopardize the subject and may require medical or surgical intervention to prevent one of the outcomes listed in this definition

Events NOT considered to be serious adverse events are:

- hospitalization for treatment, which was elective or pre-planned, for a pre-existing condition that did not worsen
- treatment on an emergency, outpatient basis for an event NOT fulfilling any of the definitions of serious given above and NOT resulting in hospital admission
- an adverse event that, had it occurred in a more severe form, might have caused death

#### Defining treatment-emergent AEs including SAEs

A treatment-emergent adverse event is ANY event that emerges during treatment, having been absent during pretreatment, or worsens relative to the pretreatment state. For the purposes of this study, treatment-emergent adverse events will be defined as those events occurring after the first dose of study drug at **Visit 4**.

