#### Safety

- comparison of treatment emergent adverse event rates between the 2, 4, 8 and 16 mg prosaptide and placebo groups
- comparison of plasma HIV RNA levels between the 2, 4, 8, and 16 mg prosaptide and placebo groups.

The safety measures will include reported/observed adverse events, vital signs, physical examination, neurological examination, laboratory safety tests, HIV-1 RNA, EKG, Karnofsky performance score, nerve conduction studies and prosaptide serum antibodies.

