## 3.1. Overall study design

This will be a randomized, double-blind, placebo-controlled multicenter study design using four dosing levels (2, 4, 8, and 16 mg/day) to evaluate the efficacy and safety of prosaptide for the relief of neuropathic pain associated with HIV-1. An interim analysis will be performed when 200 subjects complete 6 weeks of treatment.

Subjects will be washed out of **adjuvant pain medications** including anticonvulsants, antidepressants, topical analgesics and short-acting narcotics. Long acting opioid analgesics (maintained at a constant daily dose throughout the study) will be permitted in up to 20% of screened subjects at each study site. Subjects taking long-acting narcotics must have received a constant daily dose for at least 30 days prior to Visit 1. All subjects will receive a supply of **acetaminophen 500 mg caplets** as **rescue medication**. Subjects who have intolerable pain despite rescue medication are permitted to discontinue from the study at any time.

The double-blind phase will include a 6 week active treatment phase with subjects receiving one of the 4 dosing levels of prosaptide or placebo as illustrated in Figure 3-1.

Subjects who meet entry criteria, including a pain level of Gracely 0.74 log units averaged over the 2-week period between Visit 2 and Visit 3, and have completed written informed consent will be randomized into the study. Subjects randomized after the **two part** screening phase will complete a one week baseline period, then will receive one of four active treatment or placebo for a **42-day** double-blind treatment period. This will be followed by a **2-week** double-blind **crossover period**, during which subjects previously receiving active treatment will receive placebo injections. **The group receiving placebo during the 42-day double-blind treatment period will be crossed over to receive prosaptide 4 mg for 2 weeks,** forming a modified **cross-over** design*.* The purpose of the crossover period is to assess the duration of prosaptide response after discontinuation of treatment. In addition, it increases the number of subjects who receive active treatment, enhancing the ability to assess the magnitude of the placebo response, and the secondary outcome of early pain response. It also allows all subjects the opportunity to receive active therapy at some point during the study. Study visits will occur every 2 weeks during both double-blind periods.

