## 3.3. Treatments

### 3.3.1. Investigational therapy, reference therapy and rescue medication

#### Treatment plan

The treatment plan is as follows:

- At Visit 3 (see Table 3-1 under Section 3.4, designated as “**R**” column), subjects will be randomized to one of four prosaptide doses (2 mg, 4 mg, 8 mg, or 16 mg), or look-alike placebo in a double-blind manner until all opened drug blocks with the 5 dose groups have been used. Subsequently, subjects will be randomized to one of only three prosaptide doses (4, 8 or 16 mg) or placebo in a double-blind manner (see section 3.3.2).
- At Visit 4, subjects will receive one of the dosing levels of drug or placebo (double-blind treatment phase).
- At Visit 7, subjects will be “**crossed over,**” with subjects who received active drug receiving placebo and subjects who received placebo receiving 4 mg of prosaptide (double-blind crossover phase).

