#### Study drug administration

After the two phase screening procedures (see Table 3-1 under Section 3.4) and the one week baseline period have been completed, the subject will be instructed in self-administration of subcutaneous injections. The **initial dose** of study drug will be **self-administered** by the study **subject** under the **observation of site personnel**. All subjects should be observed for adverse reactions for at least 30 minutes following the initial dose of study drug. All subsequent doses will be administered at 24-hour intervals for a period of 6 weeks. If a dose is **missed by more than 12 hours, it should not be given**. If the subject **misses more than 4 non-consecutive or 3 consecutive doses of study drug in a 2-week interval, the subject should be discontinued from the study due to noncompliance**.

Subjects at designated centers will also have doses administered in clinic at Visits 6 and 7 so that accurately timed samples for PK analysis can be collected. Study drug from the previous supply, not the new box should be administered at these visits. See Section 3.8: Drug levels and pharmacokinetic assessments for details.

See Appendix 3 (Study drug administration instructions) for details of the study drug administration procedure.

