### 3.7.3. Adverse event reporting

Information regarding all adverse events, discovered by investigator, or detected through physical examination, laboratory test or other means, will be collected and recorded on the Adverse Event page of the CRF or Serious Adverse Event page of CRF and followed as appropriate. Adverse events must be reported for the entire duration of the study, not just during administration of study drug. Treatment-emergent adverse events will be listed separately in the final clinical study report.

As far as possible, each adverse event will also be described by:

- its **duration** (start and end dates),
- the **severity** grade (mild, moderate, severe),
- its **relationship** to the study drug (probably related, possibly related, and unlikely),
- and the **action(s)** taken and, as relevant, the outcome.

ANY SERIOUS ADVERSE EVENT, OR DEATH DUE TO ANY CAUSE, WHICH OCCURS TO ANY SUBJECT IN THIS STUDY OR WITHIN 30 DAYS FOLLOWING CESSATION OF TREATMENT, WHETHER OR NOT RELATED TO THE INVESTIGATIONAL PRODUCT, MUST BE REPORTED WITHIN 24 HOURS TO ONE OF THE INDIVIDUAL(S) LISTED ON THE CONTACT INFORMATION PAGE (THE SPONSOR’S REPRESENTATIVE). ALL SUBJECTS WITH SERIOUS ADVERSE EXPERIENCES MUST BE FOLLOWED UP FOR OUTCOME.

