### 6.1.6. Safety evaluation

The assessment of safety will be based mainly on the frequency of adverse events and on the number of laboratory values that fall outside of pre-determined ranges. The safety measures will also include vital signs, physical examination, neurological examination, HIV-1 RNA, EKG, Karnofsky performance score, nerve conduction studies and prosaptide serum antibodies.

Adverse events will be summarized by presenting, for each treatment group, the number and percentage of subjects having any adverse event, having an adverse event in each body system and having each individual adverse event. Any other information collected (i.e. severity or relatedness to study medication) will be listed as appropriate.

Laboratory data will be summarized by presenting shift tables using extended normal ranges (baseline to most extreme post-baseline value), by presenting summary statistics of raw data and change from baseline values (means, medians, standard deviations, ranges) and by the flagging of notable values (as defined in section 7.1) in data listings. Two (or more)-way frequency tables of changes in laboratory test results in terms of normal ranges at the follow-up visits versus baseline by treatment group, as well as changes in absolute values from baseline will be examined for treatment differences. Change from baseline of plasma HIV-1 RNA levels by treatment group will be specifically evaluated.

Data from other tests (i.e. electrocardiogram or vital signs) will be listed, notable values will be flagged, and any other information collected will be listed as appropriate. Any statistical tests performed, such as the Chi-square test and the t-test, to explore the data will be used only to highlight any interesting comparisons that may warrant further consideration.

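### Adverse event tables and laboratory shift tables have no cut at the Visit 7 crossover, so any excess risk at 4 mg would dilute the drug-versus-placebo safety comparison

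*Protocol*

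**What the plan says.** - **Window.** Section 3.7.1 states that "treatment-emergent adverse events will be defined as those events occurring after the first dose of study drug" at Visit 4. It gives no end.
- **Collection.** Section 3.7.3: "Adverse events must be reported for the entire duration of the study, not just during administration of study drug".
- **Comparison.** Section 2.4 lists as a safety endpoint the "comparison of treatment emergent adverse event rates between the 2, 4, 8 and 16 mg prosaptide and placebo groups". Section 6.1.6 presents, "for each treatment group, the number and percentage of subjects having any adverse event". Section 6.1.1 runs the safety analysis on the intent-to-treat population only, with no period-specific or as-treated set.
- **Laboratories.** Section 6.1.6 plans "shift tables using extended normal ranges (baseline to most extreme post-baseline value"). Section 3.4.2 schedules safety laboratories at Visit 8.
- **Crossover.** Randomised dosing lasts six weeks: "All subsequent doses will be administered at 24-hour intervals for a period of 6 weeks" (Section 3.3.1). At Visit 7 active subjects move to placebo, and the placebo group "will be crossed over to receive prosaptide 4 mg for 2 weeks" (Section 3.1).
- **Separate crossover summary.** The last paragraph of Section 6.1 summarises change from Visit 7 by dose group. Safety laboratories are the only safety measure it names, and adverse events are not included.

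**The concern.** The placebo arm is the only concurrent safety control. If its events are counted to the end of the study, a quarter of its nominal post-dose follow-up is on prosaptide 4 mg, while the same two weeks in each active arm are on placebo. Both changes pull the arms together. The same holds for a shift table that takes each subject's worst value: a placebo subject's worst value may arise on 4 mg and still count as placebo.

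Section 6.1.6 rests the safety assessment mainly on adverse event frequency and out-of-range laboratory values, and these are the two measures exposed. What is at stake is whether the main safety tables can show a drug-versus-placebo difference if there is one.

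**Working it through.** **Inputs.** From the protocol: 6 weeks of randomised treatment (Section 3.3.1) and 2 weeks of crossover (Section 3.1), both nominal because visits have a window of ±3 days. Assumed, because the protocol gives no event rates: constant weekly hazards h0 on placebo, h4 on 4 mg and hd on dose d, with no carry-over. The Introduction's report of a short half-life without accumulation makes the last assumption reasonable. There is no planning figure for adverse events to reproduce.

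**Share of follow-up off the randomised treatment.** 2/(6+2) = 25% in every arm.

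**Cumulative hazard, 4 mg versus placebo.**
- To the first crossover dose: 6·h4 − 6·h0 = 6(h4−h0).
- To Visit 8 by original arm: (6·h4 + 2·h0) − (6·h0 + 2·h4) = 4(h4−h0).
- Loss: 2/6, one third, whatever the rates.

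**Apparent rate ratio.** For a true ratio r it is (6r+2)/(6+2r):
- r = 1.5 gives 11/9 = 1.22
- r = 2 gives 14/10 = 1.40
- r = 3 gives 20/12 = 1.67

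**Percentage of subjects with an event, 4 mg versus placebo.** Risk = 1 − exp(−cumulative hazard). The placebo risks and rate ratios are assumptions.

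| Placebo 6-week risk | Rate ratio | 6 weeks (difference) | 8 weeks, original arm (difference) | Share kept |
|---|---|---|---|---|
| 5% | 1.5 | 7.4% v 5.0% (2.4) | 9.0% v 7.4% (1.6) | 0.65 |
| 10% | 2 | 19.0% v 10.0% (9.0) | 21.8% v 16.1% (5.7) | 0.63 |
| 20% | 2 | 36.0% v 20.0% (16.0) | 40.6% v 31.1% (9.5) | 0.60 |
| 30% | 3 | 65.7% v 30.0% (35.7) | 69.5% v 51.0% (18.5) | 0.52 |

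For placebo risks of 5% to 30% and ratios of 1.5 to 3, the 4 mg difference shrinks to 0.52–0.65 of its 6-week value.

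**Events tied to first exposure.** If 4 mg adds a 10% risk only soon after the first active dose, over a 10% six-week background, the 6-week comparison is 19.0% v 10.0%. By Visit 8 both arms have had a first exposure, so it is 21.8% v 21.8% and the difference is gone.

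**Other doses versus placebo.** The excess becomes (6·hd + 2·h0) − (6·h0 + 2·h4) = 6(hd−h0) − 2(h4−h0), a proportional loss of (h4−h0)/[3(hd−h0)]. If excess risk were proportional to dose, the loss would be:
- 2 mg: 4/(3×2) = 67%
- 4 mg: 4/(3×4) = 33%
- 8 mg: 4/(3×8) = 17%
- 16 mg: 4/(3×16) = 8%

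**Dose versus dose.** Every active arm adds the same 2·h0, so the cumulative difference between doses d and d' stays 6(hd−hd').

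**No excess at 4 mg.** With h4 = h0, the term 2(h4−h0) is zero and the cumulative excess of every dose is unchanged.

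**The case against.** **The protocol never says that crossover events are attributed to the randomised arm.** This is true. It treats the six-week treatment period and the crossover as distinct, calls Visit 7 the end of active treatment, and limits the exposure summary in Section 6.1.3 to six weeks. A period split is compatible with that, and an analysis plan not shown here could make one. What stands is that attribution to the original arm is the natural reading, not an explicit rule. But the open-ended window and the worst-value rule are stated, and an analysis plan would have to depart from both. The opening sentence of the definition, which speaks of events emerging during treatment, does not close the window, because crossover injections are also study treatment.

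**Partial mitigation exists.** Section 6.1.6 also plans laboratory tables at follow-up visits against baseline, and Section 6.1 adds the Visit 7 to 8 laboratory change. Neither removes Visit 8 from the shift tables or covers adverse events. HIV-1 RNA, EKG, Karnofsky score, nerve conduction and antibody are scheduled no later than Visit 7 (Table 3-1) and are largely unaffected. This stands in full.

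**There may be no excess risk.** The Introduction reports similar numbers of treatment-emergent events in all groups of the diabetes trial. If that holds here, nothing is diluted. A reader might infer that drug harm will be understated. The documents support this only on condition that 4 mg carries some excess. Still, a safety comparison should be able to show such an excess.

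**Dose selection.** A reader might infer that the dilution makes the similar-safety condition for the recommended dose easier to meet. It does not: the synopsis and Section 6.1.5 apply that condition among the dose groups, and all of them receive the same placebo crossover.

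**The analysis is descriptive and can be rerun.** This also stands. Section 6.1.6 uses tests only to highlight comparisons, no data are lost, and the primary endpoint is untouched.

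**Conclusion.** The point holds as a conditional bias in the drug-versus-placebo adverse event comparison and in the laboratory shift tables. On the natural reading, 25% of nominal post-dose follow-up in each arm is counted under a treatment the subject was no longer taking.

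For 4 mg the cumulative excess falls by one third, and a true rate ratio of 2.0 appears as 1.4. This assumes constant hazards, no carry-over and some excess risk at 4 mg. The fall in percentage points depends further on event rates that the protocol does not give. The 4 mg figures should not be carried over to every dose: under dose-proportional excess, itself an assumption, the loss at 16 mg is about 8%. Comparisons between active doses, and so the recommendation condition, are not affected by the placebo arm's exposure to 4 mg. The wording should be settled before the safety tables are produced.

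**What to change.** In Sections 3.7.1 and 6.1.6, limit the between-group adverse event comparison and the shift tables to the period from the first dose at Visit 4 up to the first crossover dose. The first crossover dose is a better boundary than the Visit 7 date, because subjects at the pharmacokinetic centres take a Week 6 vial in clinic at Visit 7 (Section 3.8).

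Summarise adverse events after that point, and the Visit 8 laboratories, separately by the treatment being taken: prosaptide 4 mg after placebo, and placebo after each dose.

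The cost is wording and an extra set of tables. Adverse event start dates are already collected (Section 3.7.3), and no further data or subjects are needed.

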### 3.7.2. Adverse event evaluation criteria

#### Relationship to study drug

The determination of the likelihood that the test drug caused the adverse event will be provided by the investigator. The investigator’s signature and date on the source document or case report form that supports the causality noted on the AE page of the CRF, ensures that a medically qualified assessment of causality was done. The signed document must be retained for the required regulatory time frame. The criteria below are intended as reference guidelines to assist the investigator in assessing the likelihood of a relationship between the test drug and the adverse event.

The following components will be used to assess this relationship; the greater the correlation with the components and their respective elements, the more likely the study drug caused the adverse event.

- **Exposure**: Is there evidence that the subject was actually exposed to the study drug such as: reliable history, acceptable compliance assessment, expected pharmacologic effect, or measurement of drug/metabolite in bodily specimen?
- **Time course**: Did the AE follow in a reasonable temporal sequence from administration of the study drug? Is the time of onset of the AE compatible with a drug-induced effect?
- **Likely Cause**: Is the AE not reasonably explained by another etiology such as underlying disease, other drug(s), or other host or environmental factors?
- **De-challenge**: Was the dose of study drug discontinued or reduced? If yes, did the AE resolve or improve? If yes, this is a positive de-challenge. If no, this is a negative de-challenge.

Note: This criterion is not applicable if: 1) the AE resulted in death or permanent disability, 2) the AE resolved or improved despite continuation of the study drug, or 3) the study is a single-dose drug study.

- **Re-challenge**: Was the subject re-exposed to the test drug in this study? If yes, did the AE recur or worsen? If yes, this is a positive re-challenge. If no, this is a negative re-challenge (note: this criterion is not applicable if: 1) the initial AE resulted in death or permanent disability, or 2) the study is a single-dose drug study).

IF A RE-CHALLENGE IS PLANNED FOR AN ADVERSE EVENT WHICH WAS SERIOUS AND WHICH MAY HAVE BEEN CAUSED BY THE STUDY DRUG, OR IF RE-EXPOSURE TO THE STUDY DRUG POSES ADDITIONAL POTENTIAL SIGNIFICANT RISK TO THE SUBJECT, THEN THE RE-CHALLENGE MUST BE APPROVED IN ADVANCE BY SAVIENT (THE SPONSOR) AND BY THE INDEPENDENT ETHICS COMMITTEE/INSTITUTIONAL REVIEW BOARD.

- **Consistency with the study drug profile**: Is the clinical and pathological presentation of the AE consistent with previous knowledge regarding the study drug or drug class pharmacology or toxicology?

The assessment of relationship will be reported by the investigator according to his/her best clinical judgment, including consideration of the above elements. The following scale of criteria may be used as a guidance (not all criteria must be present in order to be indicative of a drug relationship).

**Probably related to study drug:**

- there is evidence of exposure to the study drug
- the temporal sequence of the AE onset relative to administration of the study drug is reasonable
- the AE is more likely explained by the study drug than by another cause
- re-challenge (if performed) is positive
- de-challenge (if performed) is positive

**Possibly related to study drug:**

- there is evidence of exposure to study drug
- the temporal sequence of the AE onset relative to administration of the study drug is reasonable
- the AE could have been due to another equally likely cause
- de-challenge (if performed) is positive

**Unlikely related to study drug:**

- there is evidence of exposure to the study drug
- there is another more likely cause of the AE
- de-challenge (if performed) is negative or ambiguous
- re-challenge (if performed) is negative or ambiguous
- there is no temporal relationship to study drug

#### Adverse event severity (intensity)

The following definitions are to be used in grading the severity of adverse events:

**Mild**: A sign, symptom or event that is noticeable but easily tolerated. It does not significantly influence performance or prevent the subject or patient from carrying on with usual life activities. Treatment intervention may be required.

**Moderate**: A sign, symptom or event that causes enough discomfort to interfere with usual life activities. Treatment intervention may be required.

**Severe**: A sign, symptom or event that causes severe discomfort to the subject and significantly affects clinical status or the ability to perform usual life activities. Treatment intervention is warranted.

SERIOUS AND SEVERE ARE NOT SYNONYMOUS. A SERIOUS ADVERSE EVENT MUST FULFILL THE REQUIREMENTS LISTED IN THE DEFINITION.

### 3.7.3. Adverse event reporting

Information regarding all adverse events, discovered by investigator, or detected through physical examination, laboratory test or other means, will be collected and recorded on the Adverse Event page of the CRF or Serious Adverse Event page of CRF and followed as appropriate. Adverse events must be reported for the entire duration of the study, not just during administration of study drug. Treatment-emergent adverse events will be listed separately in the final clinical study report.

As far as possible, each adverse event will also be described by:

- its **duration** (start and end dates),
- the **severity** grade (mild, moderate, severe),
- its **relationship** to the study drug (probably related, possibly related, and unlikely),
- and the **action(s)** taken and, as relevant, the outcome.

ANY SERIOUS ADVERSE EVENT, OR DEATH DUE TO ANY CAUSE, WHICH OCCURS TO ANY SUBJECT IN THIS STUDY OR WITHIN 30 DAYS FOLLOWING CESSATION OF TREATMENT, WHETHER OR NOT RELATED TO THE INVESTIGATIONAL PRODUCT, MUST BE REPORTED WITHIN 24 HOURS TO ONE OF THE INDIVIDUAL(S) LISTED ON THE CONTACT INFORMATION PAGE (THE SPONSOR’S REPRESENTATIVE). ALL SUBJECTS WITH SERIOUS ADVERSE EXPERIENCES MUST BE FOLLOWED UP FOR OUTCOME.

